## **1. Background**

###### *The need to improve the sexual health of young people*

## Sexual health is integral to the health of the public and includes the prevention of sexually transmitted infections (STI) and unintended pregnancy. Important consequences of STI include pelvic inflammatory disease, infertility, cervical cancer and increased susceptibility to HIV infection. Unintended pregnancy is associated with poorer health, economic and social outcomes for both mother and child [1].

## The impetus for promoting sexual health among young people in the UK has been generated by concerns over high rates of teenage conceptions – the UK has the highest rate in Europe – and the need to control the spread of STI including HIV. National survey data indicate that first sexual intercourse is occurring at an increasingly early age [2]. The younger a person is at first sexual intercourse, the less likely it is that contraception will be used. Half of young people who are sexually active before age 16 use no contraception and half of the pregnancies in this age group end in abortion. Despite government targeting of sexual health as a key area for public health action in the UK, recent national data show worsening trends and substantial inequalities in teenage STI and pregnancy [3-4]. The UK government has recently announced a national campaign to tackle the problem of teenage pregnancy [4]. The campaign goal is to halve the number of conceptions in under 18 year olds by 2010.

*How effective is school sex education in tackling this problem?*

The great majority of young people receive some kind of sex education in school5 and the government recognises school sex education as an important strategy to promote young people’s sexual health and reduce teenage pregnancy. However, there is little systematic information about the extent to which sex education influences behaviour even though schools are the setting for much sexual health promotion work with young people. There is also wide debate about the merits of school sex education, and in parcticular whether sex education reduces or increases sexual risk behaviour [5].

Current theories of sexual health promotion emphasise concepts of empowerment, participation and mobilisation of groups and individuals to define and meet their own health needs [6]. Research into young people’s own experiences and perspectives questions the appropriateness of traditional didactic methods of teaching sex education in schools. Young people are often critical of the content and style of the sex education they receive at school. Teachers may be perceived as embarrassed and uneasy about teaching sex education [7,8]. Young people commonly report that coverage of the subjects they wanted to know about is inadequate, while subjects with which they were already familiar received too much attention [4].

*Research into the effectiveness of sexual health interventions for young people.*

Uncertainty about the effectiveness of different methods of sex education reflects a lack of scientific evaluation. The background to RIPPLE is a systematic review of sexual health promotion interventions for young people [9]. The review found 65 separate studies evaluating the outcome of interventions, of which only 12 (18%) were methodologically sound. Criteria used in evaluating the studies were based on the use of a control group, pre and post intervention measures and reporting on all outcomes included in the aims of the study. Eleven of the methodologically sound interventions were carried out in North America and one in Finland. Only two of the sound evaluations (both in North America) were able to show an impact on self-reported sexual behaviour. The review recommended that evaluation of sexual health interventions should incorporate experimental designs (randomisation), adequate sample sizes and the long term follow-up of participants.

A more recent systematic review [10] compared the results of randomised trials with observational studies of interventions to prevent adolescent pregnancy. Thirteen trials and 17 observational studies were identified. Based on four comparable outcomes (sexual intercourse, contraceptive use, responsible sexual behaviour and pregnancy), the review found that the observational studies yielded systematically greater estimates of intervention effects than randomised trials. It appeared unlikely that the interventions evaluated in the observational studies were inherently more effective than those studied in randomised trials. A more likely explanation for the findings is that adolescents assigned to the intervention in the observational studies were destined to have better outcomes than control adolescents irrespective of the intervention. In effect, the studies were probably comparing different populations rather than different interventions. The review concluded that, wherever possible, recommendations and public policy should be based on randomised trials.

*Peer-led sex education*

Peer-led health interventions are currently enjoying a wave of popularity and in July 1999 the Social Exclusion Unit report on teenage pregnancy identified peer-led sex education as a possible prevention strategy [4]. The term “peer” relates to one of equal status. Peer-led (sex) education can therefore be defined as “teaching or sharing of (sexual health) information, values and behaviours by members of similar age or status group.” [11] A number of psychosocial theories of behaviour change have been employed to provide a framework for understanding the processes involved peer led education including social learning theory [12], social inoculation theory [13] and diffusions of innovations theory [14] (see reference [15] for overview). Common to all these theories is the idea that behaviour is influenced by an individual’s social network and the normative values and beliefs that exist among friends, peers and family. Peer led programmes claim an advantage over traditional teacher-led methods through the belief that peer leaders act as positive role models with whom the target group can relate, conveying information in a way that appeals to the target group. The egalitarian nature of the interaction between young people provides the opportunity to communicate openly and discuss sexual health issues in ways that have specific social and cultural relevance. Peer leaders are viewed as credible sources of health promoting information. Such characteristics facilitate a process whereby young people acquire necessary information on sexual health and explore attitudes within a context which directly relates to their own experience of their social environment.

The rising popularity of peer education has brought the methods under particular scrutiny. A recent review of peer delivered health interventions for young people funded by the Department of Health found some evidence to support the effectiveness of peer delivered interventions but commented that the variability of different peer interventions and the scarcity of methodologically sound studies made it difficult to draw conclusions about the specific characteristics of effective peer delivered interventions. [16] In most reports the relationship between theory and intervention strategies was unclear. Studies exploring the implementation of peer led methods tended to focus on the acceptability of the intervention. Very few examined the relationship between peer leaders and their target group. Furthermore, very few studies have integrated both process and outcome evaluations. Other reviews of peer-led education have reached more negative conclusions and challenged assumptions that peer leaders are perceived as credible sources by the target group, [17] or that they model behaviours and attitudes that are necessarily compatible with the agendas of health professionals.

*Rationale for a large randomised controlled trial of peer-led sex education*

Randomised trials are recognised as the gold standard for evaluating health care interventions. Although evaluation of complex interventions, such as those aiming to change sexual behaviour, presents particular challenges, [18] the systematic comparison, described above, between trials and observational studies in adolescent pregnancy prevention confirms the need for randomised trials to strengthen the evidence base in this field of health promotion. [10] Although peer-led sex education is popular with young people, its effectiveness, in terms of health outcomes, is unknown. The use of outcome measures such as abortion rates requires a trial of sufficient sample size to detect a measurable difference in these rates. In 1993 the abortion rate in England and Wales was 22 per 1000 in women aged 16-19 years. To detect a difference of one third reduction in this rate would result in only seven fewer pregnancies per 1000 women. It is therefore important to have a study that is large enough to detect change that can be attributed to the intervention rather than chance variations in abortion rates. STD rates peak at ages 16-19 in women and later in men. Using STDs as outcome measures of an intervention implemented before 16 requires follow-up to the age of 20. Other important outcomes that occur more commonly, or can be collected more easily, include condom use at first intercourse, contraceptive use, regretted sexual encounters, knowledge, attitudes and intentional and actual sexual behaviour.

There is general agreement that effective sex education should not be measured purely in terms of health outcomes, but should also include measures of the quality of sexual relationships and perhaps the wider impact of the intervention in schools. Pupil satisfaction with sex education and their views on the appropriateness of what they receive should also receive attention. In addition, evaluation of the processes involved in implementing an intervention should be an integral part of any well-designed trial of a complex intervention. The process evaluation is key to explaining the observed outcomes and to the future implementation of a successful intervention.

*A pilot study*

The Department of Health funded a 15month pilot study for this trial that was conducted in four schools in the London area and completed in February 1997. The aim was to assess the feasibility and acceptability of conducting a large RCT, to pilot the intervention and the study methods, including baseline and post-intervention questionnaires. [19] The intervention followed a model developed by the Ibis Trust, an independent organisation with expertise in developing and implementing peer-led education programmes. The pilot study showed that the intervention needed to be modified to produce a more standardised intervention that could be evaluated in a large RCT. The pilot showed that the evaluation methods were feasible and acceptable to pupils, parents, staff and governors. [19]

In summary, peer-led sex education is clearly popular with staff and pupils, but its effectiveness, in terms of sexual health outcomes, is unknown. RIPPLE (A Randomised Intervention trial of Peer-Led Sex Education in schools in England) is a school-based randomised controlled trial in southern England designed to provide more reliable evidence about the long term impact of peer-led sex education on sexual health.

2. Trial funding, investigators, organisation and management

The trial is funded by the Medical Research Council (MRC) for five years from August 1st 1997 (Phase I), with four years additional funding for long term follow-up to ages 19-20 (Phase II) dependent on the results of Phase I.

The trial is run jointly between two academic institutions, the Department of Sexually Transmitted Diseases, at UCL and the Social Science Research Unit at the Institute of Education, and an external group of practitioners with expertise in peer-led education. The trial is therefore multidisciplinary with collaboration between clinical epidemiologists and social scientists. The Department of STD acts as the data management site and the MRC grant is administered through the Institute of Education.

**3. Aims and objectives**

The aim of the trial is to evaluate the effectiveness of school-based peer-led sex education in promoting young people’s sexual health

The primary objective is to measure the effectiveness of peer-led sex education in reducing the incidence of unwanted pregnancy, termination of pregnancy, unprotected sexual intercourse and STI, and in improving the quality of sexual relationships. Secondary objectives relate to the wider effects on school ethos, particularly on the status and implementation of sex education in schools, and on relationships between staff and students.

4. Trial design

RIPPLE is an open, stratified, cluster randomised controlled trial with extensive process evaluation as well as outcome evaluation. Intervention occurs at ages 13-14 years. In Phase 1 of the trial, students are followed-up to age 15-16; in Phase 2 follow-up of both arms is extended to ages 19 –20.

- 1. **Follow-up**

In Phase I, the first follow-up is conducted 6 months post-intervention at ages 14-15; and the second follow-up is conducted 18 months post-intervention at ages 15-16. At each follow-up information is collected by pen and paper questionnaire completed in the classroom setting. For pupils absent on the day of the survey, a questionnaire is left with the contact teacher and each absentee is invited to complete the questionnaire as soon as they return to school.

In Phase II , the third follow-up is conducted in the community at ages 17-18; the fourth and final follow-up is conducted in the community at ages 19-20. At this stage, follow-up information is collected through 1) anonymised linkage to statutory abortion and birth notifications, 2) postal questionnaire and 3) postal saliva or urine samples which will be tested for markers of STI exposure (see trial endpoints).

##### Trial endpoints

**Phase 1**: Primary endpoints are unprotected sexual intercourse before the age of 16 and regretted sexual relationships. Other phase 1 endpoints relate to the Government’s Teenage Pregnancy Strategy,[3] including pupil satisfaction with school sex education, ability to access sexual health services, condom use at first and last intercourse and appropriate use of contraception. In terms of secondary objectives, the process evaluation will identify reasons for continuing, extending or changing the method of sex education used during the study, and assess staff attitudes to future provision of sex education.

**Phase II**: Primary endpoint is cumulative incidence of termination of pregnancy by age 19-20. The Chief Medical Officer has agreed to the use of statutory abortion notifications for this purpose. Anonymised data will be obtained from the Office of National Statistics on abortions in both experimental and control schools. This means that there will be no loss to follow-up for the primary outcome. In addition to unprotected intercourse and regretted sexual relationships, phase II outcomes will include markers of exposure to STI i.e chlamydia and herpes genital infections through measurement of type specific *C. trachomatis* and Herpes simplex virus 2 antibodies respectively.

### 4.3 Inclusion and exclusion criteria

Schools in southern England are eligible to take part in the trial if they are comprehensive, mixed sex, non-selective and take pupils until age 18. Schools that are already implementing peer-led sex education are not eligible (but schools that use peer-led methods in other areas e.g. anti-bullying programmes are eligible). In each school, all pupils in Year 9 (13-14 year olds) are eligible for the study unless their parents have withdrawn them from the research study. In experimental schools, all pupils in Year 12 (aged 16-17 years) are eligible to be peer-educators, and no one who volunteers is excluded.

**4.4 Sample size and power calculations**:

The power calculation takes into account that the school, not the individual, is the unit of randomisation. [20] The number of schools required for the trial depends on 1) the expected incidence rate of the main outcome in the absence of any intervention 2) the variability in the incidence rate between schools 3) the number of participating pupils in each school 4) the magnitude of effect of the intervention that the trial is intended to detect and 5) the desired degree of certainty (statistical power) with which such an effect is to be detected. Termination of pregnancy was chosen as the primary outcome on which to estimate the size of the trial because it is an important and relatively uncommon event for which reliable data are available. Based on the legal abortion rate for 16-19 year olds in England and Wales in 1994 (23 per 1000), the expected cumulative incidence of termination by age 20 will be at least 9%. The variability in outcome between schools can be expressed as k (the coefficient of variation (SD/Mean) of the incidence rate) which, in the absence of reliable data, was assumed to be 0.2. The same variability can also be expressed as a standard deviation of 1.8% which translates into nearly 3 fold variation between schools in the abortion rate from 5% to 13%. With these assumptions, 14 schools, with an average of 150 girls in each, would be needed in each arm to detect a one third reduction in the termination rate, from 9% in control schools to 6% in intervention schools, with over 80% statistical power at 5% significance. However, the value of k, or the extent of between school variability can be reduced by effective stratification of schools (see 4.5 below), thus making the sample size estimates conservative.

The trial will have over 90% power to detect a reduction in the proportion of pupils having unprotected intercourse before age 16, from 35% to 25%, assuming a standard deviation of 8.2% which gives a range of 19% to 51% between schools. Two successive cohorts of Year 9 pupils (with average Year size 150 pupils, or 75 girls) are recruited in each school to provide adequate statistical power. Total number of participants is over 8000.

**4.5 Method of randomisation**.

The method is stratified randomisation with the school as the unit of randomisation. Before randomisation, 28 eligible schools are ranked according to a composite score developed to assess risk status. The score is based on seven factors:

1. socioeconomic status (the proportion of pupils having free school meals),
2. ethnicity (the proportion of Black and Asian students),
3. educational attainment (the proportion gaining 5 or more GCSEs),
4. continuing education (the proportion staying on after age 16),
5. the quality and quantity of current school sex education,
6. the attitude of the school towards health promotion (the availability of information and links with outside agencies, and
7. local family planning services (convenient location or opening times, youth-friendliness and level of use by students).

None of the factors is weighted with respect to the others. Information about factors 1-4 is obtained directly from school staff or from recent Ofsted reports; information about factors 5-7 is obtained directly from school staff by interview or questionnaire. After ranking by composite score, the 28 schools are divided into 3 equal sized strata of low, medium and high risk schools. Within each stratum, schools are randomised to experimental (peer-led sex education) or control (usual practice) arm, giving a total of 14 experimental and 14 control schools.

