**7.2 Analyses based on individual pupil’s outcome**

*Marginal models:*

The marginal probabilty of unprotected intercourse by age 16 and of termination of pregnancy by age 19 will be compared between the intervention and control schools using the Generalized Estimating Equations approach of Liang and Zeger. [22]

*Conditional Models:*

The probability of outcome conditional on school effect will be compared between the intervention and control arms by fitting multilevel methods with random effects for school and cohort using MLwin.

Secondary analyses will adjust the comparisons using marginal models and conditional models for pupil level covariates: sex (first primary endpoint only), ethnic origin, social class etc.

- 1. **Analysis of process data**

Data collected from focus group discussions with students and peer educators, interviews with teachers, observation of lessons and researcher field diaries are transcribed and analysed using a variety of approaches including thematic content analysis and discourse analysis. A particular challenge is to move beyond the usual practice in which 'qualitative' data are analysed separately and sit alongside 'quantitative' measures of outcome. To integrate process and outcome evaluations, qualitative process data are coded to create variables which describe the implementation and acceptability of the intervention. Data on these variables are entered into the computer database and analysed with the data from questionnaire surveys. Data from the process evaluation may also be analysed independently of the data from the questionnaire surveys to generate hypotheses about the importance and impact of local effects on outcomes in individual or groups of schools. The data will also be analysed to address other important questions, for example to describe the type of young people who volunteer to be peer educators and the impact on them of their involvement in the programme.

8 Trial Steering Committee

The trial has a steering committee whose members are:

[name] (Chair), LSHTM

[name], Head of Watford Grammar School

[name], Health Education Co-ordinator, Camden Education Department

[name], R&D Division, Department of Health

[name], MRC Sociology Unit

MRC Observer.

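### Seven school factors are measured before randomisation, but the analysis uses them only through three composite strata; one prespecified school-level covariate would recover precision, mainly for unprotected intercourse

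*Protocol*

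**What the plan says.** Protocol 4.5 sets the allocation: "The method is stratified randomisation with the school as the unit of randomisation". Before the draw, "28 eligible schools are ranked according to a composite score developed to assess risk status". The score covers free school meals, ethnicity, attainment, staying on after 16, current sex education, school attitude to health promotion, and local family planning services. On their combination the text says "None of the factors is weighted with respect to the others". Then "the 28 schools are divided into 3 equal sized strata of low, medium and high risk schools", "giving a total of 14 experimental and 14 control schools".

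Section 4.4 relies on this. It says that between-school variability "can be reduced by effective stratification of schools (see 4.5 below), thus making the sample size estimates conservative", but gives no amount.

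On analysis, 7.1 compares school rates twice, once ignoring the three strata and once using them. Section 7.2 fits GEE and multilevel models and does not name the strata. It then says: "Secondary analyses will adjust the comparisons using marginal models and conditional models for pupil level covariates", listing sex, ethnic origin and social class and leaving the list open. No school-level covariate is named in either section.

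**The concern.** With 14 schools per arm, differences between schools are a large part of the error. The trial holds seven school characteristics that were chosen because they were thought to mark risk. Collapsing them into one equally weighted score and then into three groups keeps only part of that information. A school with high free-school-meals take-up and good local services can fall in the same stratum as one with low take-up and poor services. If one factor predicts the outcome much better than the others, most of its predictive value may lie within strata, where no planned analysis uses it.

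The background section reports that "recent national data show worsening trends and substantial inequalities in teenage STI and pregnancy", and free school meals is the protocol's own socioeconomic measure, so it is a natural candidate. What is at stake is the width of the confidence intervals, and whether a school-level adjustment is chosen before or after the outcomes are seen.

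**Working it through.** **Inputs from 4.4 and 4.5.** Termination: 9% v 6%, k = 0.2, 150 girls per school. Unprotected intercourse: 35% v 25%, SD 8.2%, so k = 8.2/35 = 0.234; two cohorts of 150 give 300 pupils per school. There are 14 schools per arm.

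**Assumptions, not in the protocol.** The composite is the plain sum of seven standardised factors. The strata are 10/8/10, because 28 does not divide by three and 14:14 must be possible. The factors share a common correlation of 0 to 0.7. Free school meals correlates 0.3 to 0.7 with the school-level outcome, and the other factors act on the outcome only through it.

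**Step 1: the plan's own figure.** Use c = 1 + (1.96 + 0.84)² × [p0(1−p0)/n + p1(1−p1)/n + k²(p0² + p1²)] / (p0 − p1)².

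- Termination: the bracket is 0.000546 + 0.000376 + 0.000468 = 0.001390, so c = 1 + 12.1 = 13.1, that is 14 schools. Power with 14 is 0.85 (0.83 if one school per arm is deducted, as the +1 implies).
- Unprotected intercourse: the bracket is 0.000758 + 0.000625 + 0.010155 = 0.011538. Power is 0.94 (0.92 with the deduction).

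Both stated powers are met with k constant across arms. If instead the SD is held equal in both arms, the figures with 14 schools are 0.81 and 0.87.

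**Step 2: between-school share of the variance.**

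- Termination: 0.000468 / 0.001390 = 34%.
- Unprotected intercourse: 0.010155 / 0.011538 = 88%.

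**Step 3: how much of one factor the strata capture.** A simulation (20,000 draws per setting) ranked 28 schools on the sum, cut 10/8/10 and randomised within strata.

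| Correlation among factors | SD of arm difference in one factor | Share of imbalance variance removed (s) |
|---|---|---|
| no stratification | 0.38 | 0% |
| 0 | 0.36 | 11% |
| 0.3 | 0.31 | 31% |
| 0.5 | 0.28 | 44% |
| 0.7 | 0.25 | 57% |

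The composite itself is well balanced: SD 0.18, with a chance below 1% of differing by more than 0.5 SD. So the strata do what they were built to do, but between 43% and 89% of the variance of a single factor remains within them.

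**Step 4: gain from adding that factor as a covariate, net of the strata.** If the factor has correlation r with the school outcome, the between-school variance is about 1 − r²s after the strata and 1 − r² after the covariate as well. Estimating one slope on about 24 degrees of freedom (28 schools − 3 strata − 1 arm contrast) inflates the latter by about 1 + 1/22 = 1.045. The net gain is 1 − 1.045(1 − r²)/(1 − r²s).

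| r | s = 0.11 | s = 0.57 | Simulated range |
|---|---|---|---|
| 0.3 | 1 − 1.045 × 0.910/0.990 = 4% | 1 − 1.045 × 0.910/0.949 = 0% | 0-5% |
| 0.5 | 1 − 1.045 × 0.750/0.973 = 19% | 1 − 1.045 × 0.750/0.858 = 9% | 8-18% |
| 0.7 | 1 − 1.045 × 0.510/0.946 = 44% | 1 − 1.045 × 0.510/0.721 = 26% | 27-44% |

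The closed form and the simulation agree to within a point or so.

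**Step 5: effect on the whole variance.** Multiply by the shares in step 2. This is slightly generous, because the strata lower those shares first.

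- Unprotected intercourse: 0.88 × (8 to 18%) = 7 to 16% at r = 0.5, and 0.88 × (27 to 44%) = 24 to 39% at r = 0.7. At r = 0.5 that is worth 14/0.93 = 15.1 to 14/0.84 = 16.7 schools per arm instead of 14.
- Termination: 0.34 × (8 to 18%) = 3 to 6% at r = 0.5, and 0.34 × (27 to 44%) = 9 to 15% at r = 0.7.

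**The case against.** The other side has much in its favour.

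- **The composite is defensible.** Twenty-eight schools cannot be cross-stratified on seven factors. If school risk follows the score, prognosis is well balanced. This stands, and the strata should stay.
- **The factors are used.** A reader might infer that the seven factors are ignored after the draw. They are not: the stratified version of 7.1 carries all seven through the score. Pupil ethnic origin and social class in 7.2 also overlap with two of them, though only in secondary models and not in 7.1.
- **No bias.** A reader might infer that chance imbalance distorts the result. It does not. Between-school variance is in the 7.1 variance, the GEE and the random effects, so such imbalance is ordinary sampling error. A 0.5 SD imbalance in a factor explaining 25-50% of between-school variance shifts termination by 0.45-0.64 points and unprotected intercourse by 2.1-2.9 points. The standard errors are about 1.0 point (√(0.001390/14)) and 2.9 points (√(0.011538/14)). It would also mislead to set those shifts beside the 69% chance (uncorrelated factors) that at least one of seven factors differs by more than 0.5 SD. For one given factor the chance is 16%, falling to 4% at correlation 0.7.
- **The stated power is not wrong.** It is met without credit for stratification (step 1, constant k).
- **The choice could sit in the SAP.** This stands in part: the absence of a covariate list would be no finding. But the protocol does specify its adjustment, and specifies it as pupil-level only.
- **The strong predictor is assumed.** The background sentence concerns STI and pregnancy. It does not mention free school meals or unprotected intercourse. This stands, which is why the gain is given as a range that begins at nothing.

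**Conclusion.** The point holds as one of precision. School information already collected is used only through three strata of an unweighted composite, and the models adjust at pupil level only. On the plan's figures this matters most for unprotected intercourse (88% of variance between schools) and less for termination (34%). The recoverable part of the between-school variance, net of the strata, is little or nothing if free school meals correlates 0.3 with the school outcome, 8-18% at 0.5 and 27-44% at 0.7. The lower end of each range applies when the seven factors are strongly correlated with one another.

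The size rests on those assumed correlations, on reading the composite as a plain sum, and on 10/8/10 strata. The documents do not support the stronger conclusions that the comparison is biased, that the sample size is inadequate, or that the randomisation should have been done differently.

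**What to change.** Before outcomes are analysed, prespecify the school's free-school-meals proportion as one school-level covariate for both primary endpoints:

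- in 7.2, in the GEE and multilevel models, entered alongside the three strata;
- in 7.1, in a covariate-adjusted version of the stratified school-level comparison.

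The figure is already needed for the composite score, so it should be held for all 28 schools and needs only the school identifier to attach. The cost is one of roughly 24 degrees of freedom and a little analysis work. If the correlation with the outcome proves low, almost nothing is gained and very little is lost. Naming the covariate now also avoids choosing one later under the open list in 7.2.

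No change to the randomisation is proposed. Table II marks early stages as completed, the note to Table I describes activities in the past tense, and the background cites a July 1999 report although the first cohort was taught in summer 1998. The draw has therefore already taken place.
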